## Abstract

**Introduction:** Immune checkpoint inhibitor (ICI) therapy is markedly improving the prognosis of patients with several types of cancer. On the other hand, the growth in the use of these drugs in oncology is associated with an increase in multiple immune-related adverse events (irAEs), whose optimal prevention and management remain unclear. In this context, there is a need for reliable and validated biomarkers to predict the occurrence of irAEs in patients treated with ICIs. Thus, the main objective of this study is to evaluate the diagnostic performance of a sensitive routinely available panel of autoantibodies consisting of antinuclear antibodies, rheumatoid factor, and antineutrophil cytoplasmic antibodies to identify patients at risk of developing irAEs.

**Methods and Analysis:** A multicenter, prospective, observational, cohort study has been designed to be conducted in patients diagnosed with cancer amenable to ICI therapy. Considering the percentage of ICI-induced irAEs to be 25% and a loss to follow-up of 5%, it has been estimated that a sample size of 294 patients is required to detect an expected sensitivity of the autoantibody panel under study of 0.90 with a confidence interval (95%) of no less than 0.75. For 48 weeks, patients will be monitored through the oncology outpatient clinics of five hospitals in Spain. Immune-related adverse events will be defined and categorized according to CTCAE v. 5.0. All the patients will undergo ordinary blood tests at specific moments predefined per protocol and extraordinary blood tests at the time of any irAE being detected. Ordinary and extraordinary samples will be frozen and stored in the biobank until analysis in the same autoimmunity laboratory when the whole cohort reaches week 48. A predictive model of irAEs will be constructed with potential risk factors of immune-related toxicity including the autoantibody panel under study.

**Ethics and Dissemination:** This protocol was reviewed and approved by the Ethical Committee of the Basque Country and the Spanish Agency of Medicines and Medical Devices. Informed consent will be obtained from all participants before their enrollment. The authors declare that the results will be submitted to an international peer-reviewed journal for their prompt dissemination.

## Introduction

### Cancer and Immune Checkpoint Inhibitor Therapy

In recent years, immune checkpoint inhibitors (ICIs) have been widely used as first- and second-line treatments for several types of cancer: melanoma, renal cell carcinoma, non-small cell lung carcinoma, urothelial carcinoma, head and neck squamous cell carcinoma, and Hodgkin’s lymphoma (Postow et al., 2015; Wilson et al., 2018). The mechanism of action of these drugs consists of blocking certain immune checkpoints within the immune system, which physiologically inhibit the activation of T cells seeking to trigger an enhanced anti-tumor immune response.

T-cell activation depends on the existence of two effector signals: 1) an antigen-specific signal, which consists of the recognition through the T-cell receptor (TCR) of antigens presented by an antigen-presenting cell involving the class II major histocompatibility complex (Hennecke and Wiley, 2001); and 2) a second non-antigen-specific signal known as antigenic co-stimulation, which consists of the interaction between the CD28 receptor (located on the surface of virgin T cells) and the B7 ligand expressed by antigen-presenting cells. Once activated, T cells express cytotoxic T lymphocyte-associated antigen 4 (CTLA-4), an inhibitory molecule homologous to CD28 that also binds to B7 but with a higher affinity than CD28, thereby acting as a physiological brake on T-cell activation through the loss of the co-stimulatory signal (Sharpe, 2009). Ipilimumab, approved for the treatment of metastatic melanoma (Robert et al., 2011), and tremelimumab, pending approval for the treatment of advanced non-small cell lung carcinoma (Johnson et al., 2021), are both monoclonal antibody antagonists that target the CTLA-4 protein.

Another well-characterized immune checkpoint is programmed death cell protein 1 (PD-1), which is expressed on T, B and natural killer cells, and binds to PD-L1 and PD-L2 ligands on various tumor cells. PD-1 and its ligands, PD-L1/2, are inhibitory homologues of CD28 and B7, respectively, and hence, their interaction inhibits T-cell proliferation, promotes central and peripheral T-cell tolerance, and decreases tumor cell apoptosis (Zhang et al., 2004). Furthermore, the PD-1/PD-L pathway, which acts synergistically with CTLA-4, is crucial for the attenuation and termination of the immune response, and therefore, its dysfunction is associated with autoimmune phenomena (Sharpe et al., 2007). Currently approved PD-1/PD-L1 checkpoint inhibitors on the market include PD-1 antibodies such as nivolumab and pembrolizumab, and PD-L1 antibodies such as atezolizumab, durvalumab and avelumab.

### Side Effects of Immune Checkpoint Inhibitor Therapy: Immune-Related Adverse Events and Possible Predisposing Factors

By unblocking certain immune regulatory mechanisms, ICIs can exacerbate pre-existing autoimmune diseases (ADs) (Abdel-Wahab et al., 2018), whose prevalence is estimated to be between 3 and 8% in the general population (Davidson and Diamond, 2001; Cooper and Stroehla, 2003; Tobón et al., 2012), or induce *de novo* immune-related adverse events (irAEs) (De Velasco et al., 2017; Postow et al., 2018). Descriptions have been published of a wide variety of irAEs, both organ-specific (hypophysitis, colitis, pneumonitis, encephalitis, thyroiditis, dermatitis-rash, vitiligo, arthritis, hepatitis, myasthenia gravis) and systemic [Sjögren’s syndrome, giant cell arteritis, systemic lupus erythematosus (SLE), remitting seronegative symmetrical synovitis with pitting edema (RS3PE) syndrome, polymyalgia rheumatica, systemic vasculitis, antiphospholipid syndrome], which hamper treatment in a significant percentage of patients with an established indication for ICIs (Spain et al., 2016). On the other hand, patients with a history of ADs, some of which are considered risk factors for cancer (Trallero-Araguás et al., 2012; Bernal-Bello et al., 2017; Lazzaroni et al., 2017; Yang et al., 2017), have been systematically excluded from pivotal clinical trials on ICIs (Haanen et al., 2020). Thus, experience with the use of ICIs in patients with ADs is scarce and comes from post-marketing observational studies (Johnson et al., 2016; Donia et al., 2017; Menzies et al., 2017; Tang et al., 2021). Despite this barrier to patients with ADs accessing treatment with ICIs, several studies suggest that the response rate is higher in patients with irAEs than those without irAEs (Attia et al., 2005; Teulings et al., 2015; Judd et al., 2017; Fujii et al., 2018; Kostine et al., 2018; Maher et al., 2019; Hussaini et al., 2021). In contrast, immunosuppressive treatment aimed at controlling irAEs may reduce the anti-tumor effect of ICIs, by “immune dampening” (Weber et al., 2016; Kim et al., 2017; Bai et al., 2021). Overall, there is a need for better clinical and immunological characterization of patients who develop irAEs.

Besides the risk of immune-related toxicity due to pre-existing ADs, other factors that may predict the occurrence of irAEs in patients receiving ICIs have yet to be identified. From a pathogenic point of view, ADs arise from an excessive response of the adaptive immune system against self-expressed antigens (autoantigens), resulting in the proliferation of B cells and generation of autoantibodies. Specifically, these autoantibodies are synthesized by memory B cells and long-lived plasma cells because of their interaction with follicular helper CD4 T (Tfh) cells in the germinal centers of secondary lymphoid organs, with the involvement of the PD-1 pathway as a promoter (Zamani et al., 2016). Apart from acting as an inhibitory signal in the T response, PD-1 also modulates the selection and survival of B cells in germinal centers, which is essential for the genesis of long-lived plasma cells (Good-Jacobson et al., 2010) through Tfh cells, which are responsible for the maturation and activation of B cells (Eivazi et al., 2016). Indeed, it has been suggested that the proportion of circulating PD-1-expressing Tfh cells is an indicator of aberrant germinal center activity leading to B hyperactivation and autoantibody generation in SLE patients (Choi et al., 2015; Xu et al., 2015). The frequency of follicular regulatory T cells, which in turn inhibit Tfh proliferation, correlates with anti-DNA levels and lupus activity (Xu et al., 2017). Nonetheless, this PD-1-mediated interaction between B cells and T cells (namely, Tfh cells) depends on a complex and subtle balance, and any dysfunction in this balance may cause autoimmune phenomena. Blockade of PD-1 and PD-L1 (but not PD-L2) promotes the expansion of the Tfh population and the antigen-specific humoral response. PD-1 deficiency leads to a lupus-like syndrome involving arthritis and proliferative glomerulonephritis (Nishimura et al., 1999). In murine models of lupus nephritis, treatment with PD-1 inhibitors reduces CD4+ PD1+ cell count and overall mortality rate, while PD-L1 inhibition increases inflammatory cytokines and autoantibody titers and accelerates renal damage (Kasagi et al., 2010). The presence of (endogenous) anti-PD-1 autoantibodies has also been reported to be associated with increased SLE activity, especially in newly diagnosed patients (Shi et al., 2017). Although all these data suggest the involvement of PD-1 in B-cell-orchestrated humoral immunity, it is currently unknown whether the mechanism by which ICIs lead to irAEs depends on the pre-existence or *de novo* generation of autoantibodies as a preliminary step for the development of toxicity (Cooling et al., 2017; Läubli et al., 2017; Osorio et al., 2017; Yoest, 2017). A further difficulty is that potentially pathogenic autoantibodies may be present in patients with irAEs but at lower levels than those commonly used as a cut-off point for clinical purposes (Yoest, 2017).

### Diagnostic Tests Used in Autoimmune Diseases: Antinuclear Antibodies, Rheumatoid Factor, and Antineutrophil Cytoplasm Antibodies

Among the various types of autoantibodies employed in clinical practice, antinuclear antibodies (ANAs) are the most widely used. These are a heterogeneous group of autoantibodies directed against one or more antigens usually located in the cell nucleus (DNA, nucleosomes, histones, ribonuclear proteins, etc.) but also occasionally in the cytoplasm (actin, vimentin, cytokeratins, histidyl-tRNA synthetase). Due to their high sensitivity, ANA detection is considered the first level test for laboratory diagnosis of ADs with systemic involvement (Agmon-Levin et al., 2014). The measurement of ANAs should be guided by clinical suspicion since as much as 5% of the asymptomatic adult population tests positive for ANAs at a titer of 1:160 (Gordon et al., 2018). Nowadays, the gold standard method for ANA screening is the indirect immunofluorescence assay (IFA), which has the advantage of providing immunofluorescence patterns suggestive of specific antibodies [see International Consensus on ANA Patterns (ICAP) in website www.ANApatterns.org (Damoiseaux et al., 2015; Chan et al., 2022)]. In the event of ANA positivity and depending on the IFA pattern, it is recommended to test for double-stranded DNA (dsDNA) and extractable nuclear antigens (ENAs), which are associated with certain ADs or some of the unique clinical manifestations of such diseases. Both ANAs and some types of ENAs (e.g., anti-Ro antibodies, specific but not exclusive to Sjögren’s syndrome, or anti-M2 antibodies, specific to primary biliary cirrhosis) may precede the diagnosis of a particular AD by several years (Jones, 2000; Jonsson et al., 2013; Hu and Deng, 2014; Theander et al., 2015). In the case of SLE, a progressive accumulation of increasingly specific autoantibodies has been described, preceding disease onset by years in individuals who are still asymptomatic (Arbuckle et al., 2003; Olsen and Karp, 2014). A working hypothesis is that ICIs, by removing the brake on inhibitory proteins, could at the same time accelerate the process of autoantibody aggregation observed in previous studies.

In recent years, one of the best characterized irAEs has been inflammatory arthritis (Belkhir et al., 2017; Kostine et al., 2018; Smith and Bass, 2019). Some expert groups have proposed specific algorithms for patients treated with ICIs who develop inflammatory arthritis recommending the measurement of rheumatoid factor (RF) and anti-citrullinated peptide antibodies (ACPAs) (Naidoo et al., 2017), both biomarkers with proven diagnostic and prognostic value in rheumatoid arthritis. Rheumatoid factors, generally of the immunoglobulin M isotype, antibodies against the constant fraction of immunoglobulin G, are more sensitive than ACPAs for the diagnosis of rheumatoid arthritis (75–80% versus 50–75%) and correlate with severe and extra-articular forms of the disease. In contrast, ACPAs offer higher specificity, in some series exceeding 90% (Nishimura et al., 2007; Payet et al., 2014), which is especially useful in the differential diagnosis of early or undifferentiated polyarthritis (Avouac et al., 2006; Whiting et al., 2010). In patients with rheumatoid arthritis, increased soluble PD-1 is known to be associated with disease activity, autoantibody titers (both RF and ACPA) and progression of radiological damage (Greisen et al., 2014). Nonetheless, in other studies including patients with ICI-induced inflammatory arthritis, ANA, RF or ACPA positivity is inconsistent. Therefore, the hypothesis that immune-related arthritis is mediated by autoantibodies remains to be confirmed.

Another group of autoantibodies useful in the diagnosis of systemic ADs are antineutrophil cytoplasmic antibodies (ANCAs) for systemic necrotizing small vessel vasculitis, also called ANCA-associated vasculitis. As with ANA and ENA screening, two complementary laboratory techniques are widely used for the detection of ANCAs: 1) IFAs (Savige et al., 2005), which are more sensitive and, in case of positivity, provide patterns with clinical correlates that add diagnostic value to the result, while allowing the exclusion of atypical ANCA patterns suggestive of conditions other than vasculitis (ANCA induction by drugs or infections, ulcerative colitis, autoimmune hepatitis, primary sclerosing cholangitis); and 2) enzyme-linked immunosorbent assays (ELISAs), which are a more specific method to confirm or rule out reactivity to disease-relevant target antigens associated with unique clinical forms of ANCA vasculitis and to monitor treatment response and risk of recurrence. There is evidence that certain CTLA-4 and PD-1 polymorphisms may promote T-cell hyperreactivity and contribute to the pathogenesis of some vasculitides (Slot et al., 2008). It has also been reported that dysfunction of the PD-1/PDL-1 pathway may be involved in the development of forms of vasculitis other than those associated with ANCAs (Watanabe et al., 2017) or inflammatory vasculopathy in general (Weyand et al., 2018). In addition, an atypical ANCA pattern, present in certain ADs of the digestive tract, could be useful as a marker for some of the most common irAEs such as colitis, hepatitis, and cholangitis.

### Summary

We are currently witnessing an exponential increase in publications on irAEs; most of them focus, however, on identifying predictors of efficacy rather than toxicity (Hopkins et al., 2017). Nevertheless, recent years have seen the emergence of several methods seeking to achieve early detection of irAEs (Patil et al., 2018; Nakamura, 2019; von Itzstein et al., 2020), namely, analysis of lymphocyte subpopulations (Das et al., 2018), autoantigen microarrays (Gowen et al., 2018; Tahir et al., 2019), molecular omics data (Jing et al., 2020), gene signatures and polymorphisms (Friedlander et al., 2018; Abdel-Wahab et al., 2021), and the gut microbiome (Dubin et al., 2016). All these still experimental tools share the drawback of a high level of complexity, limited availability, and high cost. In parallel, other more accessible risk factors and markers have been suggested, namely, female sex (Valpione et al., 2018), total white blood cell and lymphocyte counts (Fujisawa et al., 2017), peripheral eosinophilia (Chu et al., 2020), sarcopenia (Daly et al., 2017), vitamin D deficiency (Bersanelli et al., 2017) and levels of more easily measurable interleukins (ILs) such as IL-6, IL-17 and IL-10 (Sun et al., 2008; Tarhini et al., 2015). Overall, there is a need for better clinical and immunological characterization of patients who develop irAEs, especially those with pre-existing ADs. Despite systematization efforts (Haanen et al., 2018; Schneider et al., 2021), it remains unclear how best to manage irAEs, and to tackle this question, there is a need to thoroughly understand the duality between the anti-tumor and the immunogenic effects of ICIs.

For all these reasons, the AUTENTIC study aims to investigate the usefulness of a sensitive, accessible, and inexpensive panel of autoantibodies, consisting of ANAs, RF, and ANCAs, to detect patients at risk of developing irAEs induced by ICIs. We also aim to describe the autoantibody profile, the potential early appearance or aggregation of autoantibodies over time, and the impact of irAEs on cancer-related survival of patients receiving ICIs.

## Methods and Analysis

### Objectives

#### Primary Objectives

• To identify predictive factors of irAEs at week 48 after the initiation of ICI therapy• To evaluate the diagnostic properties (sensitivity, specificity, positive predictive value, negative predictive value, likelihood ratios) of a predictive model of irAEs.

#### Secondary Objectives

• To describe the profile of detectable autoantibodies over a 48-weeks follow-up in patients with cancer treated with ICIs, regardless of whether they develop irAEs• To compare irAE-free survival among patients positive for autoantibodies before ICI initiation, patients positive for autoantibodies after ICI initiation and patients negative for autoantibodies throughout follow-up• To analyze cancer-related survival in patients treated with ICIs who develop irAEs and compare it with that in patients who do not develop irAEs• To investigate the potential early appearance and/or aggregation of autoantibodies over time up to the time of irAEs diagnosis.

This study protocol corresponds to the first phase of the AUTENTIC project, which will be followed by an external validation of a predictive model of irAEs with prospective data in an independent cohort of patients.

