### Endpoints

The primary endpoint of the study will be the proportion of patients developing at least an irAE at week 48 after the initiation of ICI therapy. An irAE was defined as any symptom, sign, syndrome, or disease caused by an immune-activating mechanism during the administration of an ICI once other causes such as an infectious disease or tumor progression have been ruled out.

Key secondary endpoints will be irAE-free survival, progression-free survival, cancer-related survival and overall survival. Other secondary outcomes will be proportion of ICI withdrawal due to the occurrence of irAEs, time to autoantibody appearance and number of positive autoantibodies included in the panel at week 48 after the initiation of ICI therapy.

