### Follow-Up Methods

Once enrolled in the study, patients will be monitored following standard recommendations. In accordance with clinical practice guidelines (Schneider et al., 2021; Schneider et al., 2022), all patients will be assessed in a treatment planning visit at baseline. In this initial visit, attending physicians will take a detailed personal and family history focused on ADs, chronic infectious and organ-specific diseases, and conduct a physical examination. In addition, to guide their care, patients will undergo a baseline blood test including a complete blood count, measurement of glucose and thyroid stimulating hormone (TSH) levels and lipid profile, renal and liver function tests, coagulation tests, and serological tests for hepatitis B and C viruses and HIV.

The frequency of follow-up will depend on the treatment schedule of each specific ICI, discretion of the attending physician and occurrence of complications (irAEs, non-immune-related toxicity, infections). All patients will have direct telephone access to the investigators in order to report early symptoms potentially related to the occurrence of irAEs*.* Treatment schedules of the ICIs will be classified into every 2 or 3 weeks up to week 12; thereafter, drug administration may be spaced out to every 4 or every 6 weeks, respectively, according to the drug data sheets.

Two types of blood samples will be taken for research purposes only: ordinary samples, defined as those drawn routinely as scheduled (Figure 1 and Figure 2), and extraordinary samples, defined as those taken at the time an irAE is detected. As far as possible, ordinary blood samples will be collected at the same time as blood draws for medical purposes before the administration of each ICI dose, in accordance with the study schedules (Figures 1, 2).

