#### Ordinary Samples and Study Schedules

Prior to receiving the first dose of ICI, all patients will undergo a baseline (i.e., week 0) blood test for research purposes, at the same time as their baseline blood test for medical purposes.

For ICIs administered every 2 weeks (nivolumab, avelumab, and durvalumab), sequential blood tests will be performed per protocol at weeks 2, 6, 12, 24, 36 and 48 after ICI initiation, all of them at the same time as draws for medical purposes (Figure 1). In other words, four ordinary samples will be obtained in the first 12 weeks (i.e., at 0, 2, 6, and 12 weeks after ICI initiation). Thereafter, the ordinary blood sampling interval will be every 12 weeks up to the end of follow-up at week 48.

For ICIs or combinations of ICIs administered every 3 weeks (ipilimumab plus nivolumab, pembrolizumab, and atezolizumab), sequential blood tests will be performed at weeks 0, 3, 6, 12, 24, 36 and 48 after ICI initiation, all of them at the same time as draws for medical purposes (Figure 2). In other words, four ordinary samples will be obtained in the first 12 weeks (i.e., at 0, 3, 6, 12 weeks after ICI initiation). Thereafter, the ordinary blood sampling interval will be 12 weeks up to the end of follow-up at week 48.

In the event of a delay in the administration of an ICI dose due to any eventuality other than an irAE, the ordinary sample corresponding to that treatment cycle will not be obtained. If the delay is due to the occurrence of an irAE, then an extraordinary sample will be obtained, as per protocol (see “*Extraordinary samples*” in the next section). Once treatment resumes, the ordinary sample corresponding to that treatment cycle will be collected per protocol.

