Survival will be assessed using a Kaplan-Meier analysis and compared between groups using the log-rank Mantel-Cox test. A subgroup analysis according to tumour type and extent of cancer (local, advanced, and metastatic disease) will be performed to assess survival outcomes*.* A multivariate analysis using logistic regression and Cox regression will be performed to detect factors associated with the occurrence of irAEs. Applying a manual backward stepwise procedure, a multivariate model will be constructed from variables that either have a p-value of less than 0.10 in the univariate analysis or are considered relevant to the dependent variable on the basis of previous studies (e.g., sex and age of patients, type of ICI). Variables not reaching statistical significance will be dropped from the final predictive model. The sensitivity, specificity, positive predictive value, negative predictive value, and probability ratios with their corresponding 95% confidence intervals of the model will be calculated. The diagnostic accuracy of the predictive model inferred from the logistic regression model will be described with the area under the receiver operating characteristic curve.

Two-sided hypothesis tests will be performed, and the significance level will be set at 5%. The statistical analysis will be conducted using IBM SPSS Statistics software version 27.0 (Chicago, IL).

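### irAE-free survival is compared between groups defined partly by later antibody results, which opens a key secondary comparison to immortal-time and outcome-dependent-sampling bias

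*Protocol article*

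**What the plan says.** The Protocol article, Secondary Objectives, sets three groups for irAE-free survival: positive for autoantibodies before ICI initiation, "patients positive for autoantibodies after ICI initiation and patients negative for autoantibodies throughout follow-up". Endpoints gives this outcome key status: "Key secondary endpoints will be irAE-free survival, progression-free survival, cancer-related survival and overall survival".

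The method is in Sample Size Calculation and Statistical Analysis: "Survival will be assessed using a Kaplan-Meier analysis and compared between groups using the log-rank Mantel-Cox test". The same section adds: "A multivariate analysis using logistic regression and Cox regression will be performed to detect factors associated with the occurrence of irAEs". Neither sentence mentions a landmark, time-updated antibody status, or a limit to samples taken before the irAE.

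Setting and Duration makes inclusion coincide with ICI start. Variables counts progression-free and overall survival from that date. irAE-free survival is not defined there, so reading it from the same origin is an inference, though a natural one.

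The sampling rules are:
- **Schedule.** On the 3-weekly regimen "sequential blood tests will be performed at weeks 0, 3, 6, 12, 24, 36 and 48 after ICI initiation". The 2-weekly regimen differs only in using week 2 in place of week 3.
- **Link to dosing.** As far as possible, ordinary samples are "collected at the same time as blood draws for medical purposes before the administration of each ICI dose" (Follow-Up Methods).
- **Delay not due to an irAE.** In that case "the ordinary sample corresponding to that treatment cycle will not be obtained" (Ordinary Samples and Study Schedules).
- **irAE.** Each one triggers an extra sample tested with the same panel (Extraordinary samples). Ordinary sampling restarts when treatment resumes. Patient Safety allows ICI to be continued, paused or stopped permanently.

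**The concern.** A patient cannot be placed in the late-positive or never-positive group at ICI start, because the label is assigned by looking forward. Two mechanisms then link the label to the outcome.

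- **Immortal time.** A patient who dies early, or whose sampling ends with an early irAE, has few chances to turn positive and tends to be labelled never-positive. A patient labelled late-positive must have remained under sampling long enough to be found positive. This makes seroconverters look protected.
- **Outcome-dependent sampling.** A delay for another reason removes a test, while an irAE adds one. A positive result found only in the irAE-triggered sample places an event in the late-positive group and pushes the other way.

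Every pairwise contrast among the three groups includes at least one group defined by later results. The contrast at stake is the one that speaks to antibodies developing on treatment, which Table 1 presents as part of this study's design.

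**Working it through.** **The plan's own figure.** No figure is given for irAE-free survival. The sample size follows from 70 / 0.25 = 280, 280 − 70 = 210, and 280 × 1.05 = 294. It rests on the sensitivity of the panel and plays no part in this point.

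**Inputs.** From the documents: 25% irAE by week 48, 280 evaluable patients, and the sampling schedule. Assumed: 20% positive at baseline, leaving 0.80 × 280 = 224 baseline-negative patients; seroconversion of 20–40% by week 48; death or dropout of 0–50%; constant hazards; persistent positivity unless stated otherwise. The cited melanoma study, with a wider battery, saw up to 19.2% for some antibodies. That is only a rough guide to seroconversion here.

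**Hand check with no true relation (30% seroconversion, no deaths, irAE as the only event).**

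1. Expected irAEs: 224 × 0.25 = 56. Without irAE: 168, of whom 30% (50.4) turn positive and 117.6 do not.
2. Cumulative hazards to week 48: irAE H = −ln 0.75 = 0.2877; seroconversion S = −ln 0.70 = 0.3567.
3. Probability of seroconverting and then having an irAE by week 48: 0.25 − [H/(H+S)] × (1 − 0.75 × 0.70) = 0.25 − 0.4465 × 0.475 = 0.0379. As a share of irAE patients this is 0.0379 / 0.25 = 15.2%.
4. The approximate HR is ln(1 − risk in late-positive) / ln(1 − risk in never-positive).

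| Sampling after the irAE | irAE patients labelled positive | irAE risk, late-positive | irAE risk, never-positive | HR |
|---|---|---|---|---|
| Stops for all | 15.2% (8.5 of 56) | 8.5/58.9 = 14.4% | 47.5/165.1 = 28.8% | 0.46 |
| Stops for half | (15.2% + 30%)/2 = 22.6% (12.65) | 12.65/63.05 = 20.1% | 43.35/160.95 = 26.9% | 0.71 |
| Continues unchanged | 30% (16.8) | 16.8/67.2 = 25% | 39.2/156.8 = 25% | 1.00 |

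The antibody has no effect in any row. Only the sampling rule changes.

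**Simulation with no true relation** (224 baseline-negative patients, 400 to 1000 runs per scenario, two-sided 5% log-rank test, irAE-triggered sample included):

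| Scenario | HR as planned | Type I error |
|---|---|---|
| irAE only, sampling ends at first irAE | 0.47–0.58 | 20–81% |
| irAE only, half of irAE patients stop | 0.69–0.77 | 6–29% |
| irAE only, sampling continues | 1.00–1.03 | about 5% |
| irAE or death (20% or 50% death, 30% seroconversion), all sampling rules | 0.49–0.71 | 30–98% |
| of which sampling continues | 0.57–0.71 | 30–87% |
| Random 5% positivity per sample, irAE only, sampling stops | 0.71–0.73 | 9–17% |
| Random 5% positivity per sample, irAE only, sampling continues | 1.18–1.20 | 8–10% |

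A separate simulation (20–30% seroconversion, 0–30% death) gave 0.43–0.46, 0.71–0.74 and 0.96–1.02 for the first three rows, and 0.39–0.63 when death counts as an event.

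**After correction.** With patients counted as positive only from their first positive sample, the null HR returns to 0.95–1.06 and type I error to about 3–8%, which is 5% within simulation noise.

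**The case against.** The strongest reply is that the bias need not arise. Ordinary sampling restarts when treatment resumes, so a patient can have an irAE, seroconvert afterwards and still be labelled late-positive. If all irAE patients are sampled on schedule to week 48, positivity persists and irAE is the only event, the null HR is about 1.0. The documents do not give the share of patients who stop ICI. This stands, and it makes the size conditional. It does not remove the problem, because sampling is tied to doses and an irAE may end dosing.

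A second reply is that an unshown analysis plan may code positivity as time-dependent in the Cox model. It may, but that model is stated for factors associated with irAEs. The never-positive group is written into the objective, so a cure would have to depart from it. The fourth secondary objective limits antibody timing to the period before irAE diagnosis; the second does not.

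Two stronger readings are tempting. A reader might infer that sampling duration, rather than the antibodies, would drive the result. The documents do not support that, because the distortion mixes with any true effect and can be nil.

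A reader might also infer that the design could make antibodies look harmful by a large factor. Hazard ratios of 1.5–3.7 appear only if 20–40% of irAE-triggered samples are assumed to turn positive because of the event. Nothing in the documents supports that figure, and such a reaction would be a real association with reversed timing, not the absence of one. With random positivity alone the upward shift is 1.18–1.20.

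**Conclusion.** The concern holds in conditional form. The comparison as written uses groups defined partly by the future and is open to immortal-time and outcome-dependent-sampling bias.

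With no true relation, the late-positive versus never-positive HR runs from about 0.45–0.6 when sampling ends at the first irAE, through 0.7–0.8 when half stop, to about 1.0 when sampling is unaffected and irAE is the only event. If death also counts, which the article does not say, the HR is about 0.4–0.7 across the sampling rules and remains below 1 even with continued sampling. Positives found only in the irAE-triggered sample act in the opposite direction, by an amount the documents do not fix. Seroconversion, death, dropout and the share who stop sampling are all assumptions.

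This affects a key secondary endpoint and should be fixed. The primary endpoint and the 294 patients are untouched. A week-0 positive versus week-0 negative contrast is free of the problem.

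**What to change.** Replace the three-group log-rank test with two analyses:

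- (a) Week-0 positive versus week-0 negative, from ICI start.
- (b) Among week-0 negatives, a Cox model with the first positive ordinary sample before irAE onset as a time-dependent covariate. If a figure is wanted, add a landmark curve.

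Do not use irAE-triggered samples, or any later sample, to form groups; report them descriptively. State whether death is an event in irAE-free survival.

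Only the analysis wording changes. The panel is run after the whole cohort reaches week 48, so the change can be made before any result is seen.

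There are three costs. Three curves from time zero are no longer available. A landmark drops irAEs that occur before it. Analysis (b) will be imprecise: by the formula in the working, with no true effect, only 0.0379 × 224 = 8.5 irAEs are expected after seroconversion at 30% (about 5.5 at 20% and 11.6 at 40%), and fewer after an observed positive ordinary sample. With 8.5 and 47.5 events, the approximate 95% limits are the HR divided and multiplied by exp(1.96 × √(1/8.5 + 1/47.5)) = 2.1.
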